### Methods for additional analyses (e.g., subgroup analyses) {20b}

In this trial, our primary objective was to assess the effectiveness of a novel core training approach for patients with stroke compared to a conventional training approach, using a simple comparative trial design to establish the superiority of one treatment group over the other. As the trial design is straightforward and robust, with no apparent confounding factors or subgroups, no additional subgroup or correction analysis is deemed necessary.

### Methods in analysis to handle protocol non-adherence and any statistical methods to handle missing data {20c}

If the patient has been receiving the intervention for more than 2 weeks, the patient’s data should still be recorded and counted.

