### Trial design {8}

To evaluate the efficacy of combining DBM with ADIM in patients with stroke, a randomized controlled trial utilizing a parallel design and employing an assessor-blinded methodology will be conducted. Participants are all inpatients of the Neurorehabilitation Department of Shanghai Second Rehabilitation Hospital who correspond with the inclusion criteria. The research projects are registered with the Chinese Clinical Trials Registry (ChiCTR-2100054897), and the study has been approved by the Ethics Committee of the Shanghai Second Rehabilitation Hospital (Shanghai, China). All participants will be informed of the trial and will sign a written informed consent form.

Patients who meet the inclusion criteria will be randomly grouped after basic data collection. This will be done by using a computer-generated random number table to randomly divide the subjects into a control group (receiving 4 weeks of conventional rehabilitation without other specific exercise interventions), and a study group (receiving 4 weeks of DBM + ADIM intervention alongside conventional rehabilitation) in a 1:1 ratio. Random numbers will be placed in opaque envelopes by independent persons not involved in this experiment to achieve allocation concealment. As this study uses an exercise intervention, it will be difficult to conceal the grouping from the therapist and subjects, but it will be possible to blind the outcome indicator measurer. We will arrange for a new assessor to replace the assessor familiar with allocation to achieve single blinding.

In this trial, a superiority trial framework has been established to examine a specific core training approach, with the aim of improving walking function in patients with stroke. The trial process includes an initial assessment one week before the start date, a final assessment post-trial, and a follow-up evaluation six months later. These evaluations serve the purpose of measuring treatment effectiveness, assessing potential side effects, and documenting relevant baseline data and clinical information of the participants. The study procedure is shown in Fig. 1 and the period of the study in Fig. 2. The program follows the principles of SPIRIT 2013.

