### Plans to promote participant retention and complete follow-up {18b}

The present study proposes several viable avenues for enhancing participant recruitment and bolstering follow-up rates. Additionally, the protocol entails the meticulous collection of outcome data for those individuals who deviate from the designated treatment regimen or withdraw from the study group altogether:A transparent and easily comprehensible trial prospectus, accompanied by a comprehensive informed consent form, is imperative for any clinical trial. The trial prospectus must furnish an unambiguous and detailed account of the trial’s purpose, methodology, and rights of the participants, to ensure that the participants are privy to the full corpus of information related to the trial’s conduct. Furthermore, the informed consent form must explicate participant obligations and rights, while concurrently clarifying any ambiguities that may arise during the trial.Friendly subject recruitment and screening process. During the recruitment and screening process, explain and ask questions in a friendly and welcoming manner to help subjects dispel their doubts and concerns while minimizing the cost of time and effort to the subjects.The habitual persuasion of patients to undergo the intervention amidst the clinical trial.Developing a rigorous and efficacious follow-up program.Collection of outcome data after subjects have withdrawn or changed treatment regimens: If the patient has been receiving the intervention for more than 2 weeks, the patient’s data should still be notes and statistics.

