### Data management {19}

During the test, what is recorded in the CRF should be true and accurate. The CRF must comply with the following criteria:The data must be recorded in black marker and the assessor’s signature is required;If the patient has been receiving the intervention for more than 2 weeks, the patient’s data should still be notes and statistics;If there is an error in the record that needs to be rectified, the recorder should draw a horizontal line under the original record and then sign the revision with the date of the correction.

Note that it is important to ensure that the original record is identifiable after the correction is made.

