There are still some limitations to this study due to some objective reasons: (1) strict control of inpatients in hospitals due to the epidemic situation, with a relatively homogenous source of subjects; (2) the ADIM technique is slightly difficult to operate and subjects have difficulty understanding the treatment; (3) unlike medication, rehabilitation training necessitates technical expertise and therapist guidance, making it challenging to implement double-blind protocols.

To adequately address the aforementioned limitations and minimize experimental errors, this study will implement the following measures: (1) it is difficult to conduct multicenter studies under strict epidemiological control, and when collecting cases in our hospital, we try to collect patients with stroke with different causes that meet the inclusion criteria; (2) multiple pre-intervention educations on ADIM techniques for therapists and subjects; (3) to minimize potential bias in trial outcomes, distinct personnel will be assigned for trial randomization and outcome assessment, ensuring the maintenance of single blinding.

Patients with stroke often have reduced trunk stability due to a lack of core strength, which in turn impairs walking function. To address this issue, our trial aims to focus on activating two critical core muscle groups, namely the diaphragm and transversus abdominis, through a combination of DBM and ADIM. Based on this training, which increases abdominal pressure and improves trunk stability, this trial will further investigate the extent to which this training improves balance and walking function in patients with early to mid-stroke.

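### The more-than-2-weeks rule implies that randomised patients who leave earlier are neither followed up nor analysed, which leaves the superiority comparison open to bias of unknown size and direction

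*Protocol article*

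**What the plan says.** Item 20c of the protocol article, the section for non-adherence and missing data, consists of one sentence: "If the patient has been receiving the intervention for more than 2 weeks, the patient’s data should still be recorded and counted".

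The same threshold appears twice more:
- Item 19 (data management) lists it among the criteria for the case report form: "If the patient has been receiving the intervention for more than 2 weeks, the patient’s data should still be notes and statistics".
- Item 18b (retention and follow-up) applies it to outcomes after withdrawal: "Collection of outcome data after subjects have withdrawn or changed treatment regimens: If the patient has been receiving the intervention for more than 2 weeks".

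Item 18b opens more broadly. It announces "meticulous collection of outcome data for those individuals who deviate from the designated treatment regimen or withdraw from the study group altogether", with no time limit.

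Item 8 sets the study-group treatment as "receiving 4 weeks of DBM + ADIM intervention alongside conventional rehabilitation", so the threshold falls halfway through treatment. The same item describes a 1:1 superiority trial in which patients and therapists know the allocation and only the outcome assessor is blinded.

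**The concern.** A condition that admits data after more than 2 weeks, with the word still, separates two kinds of leaver. Those past the threshold stay in. No provision is made for the others, and the natural reading is that they are left out. Whether a patient is counted would then depend on something that happens after randomisation and that allocation can influence, since patients and therapists are unblinded. The groups compared would no longer be the groups randomised.

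The rule covers collection as well as analysis: item 20c speaks of recording, item 19 concerns the case report form, and item 18b concerns outcomes after withdrawal. If the 4-week walking test is never recorded for early leavers, a later analysis plan cannot restore it. This is therefore a rule the protocol fixes badly, and more than a detail left to another document.

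**Working it through.** **1. The three statements and the promise, side by side.** Items 18b, 19 and 20c carry the same condition. None says what happens at 2 weeks or less, and no other section fills the gap. The opening of item 18b has no time limit, while its concrete rule has one. Read as a limit, the rule narrows the promise. Read as a minimum, it leaves early leavers unaddressed. Either way the wording needs correcting.

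**2. The plan's own figures.** Item 14 gives a standardised effect of 1.1327272, power 0.9, alpha 0.05, 36 cases, 15% attrition and a final 42. Item 20a makes the tests two-sided.
- Two-sample t-test, noncentral t: 17 per arm gives power 0.893 and 18 per arm gives 0.910, so 2 × 18 = 36. Reproduced.
- 36 × 1.15 = 41.4, rounded up to 42. Reproduced. (36 / 0.85 = 42.4 would round up to 43; the difference is immaterial here.)
- Per arm: 42 / 2 = 21. Expected losses: 0.15 × 42 = 6.3, about 6, over the whole trial and both arms.

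**3. Shift in the study-arm mean if early leavers are left out.** Let k of 21 study-arm patients leave by 2 weeks, and let their mean outcome be δ SD worse than that of the patients who stay. Then:

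mean of all 21 = mean of stayers − (k/21) × δ

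so the stayers overstate the arm mean by (k/21) × δ. Both k and δ are assumptions; the documents give neither. The control arm is assumed to have no matching loss.

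| k | δ = 0.5 SD | δ = 1.0 SD |
|---|---|---|
| 3 | 3/21 × 0.5 = 0.071 | 3/21 × 1.0 = 0.143 |
| 5 | 5/21 × 0.5 = 0.119 | 5/21 × 1.0 = 0.238 |

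Against the planned effect of 1.133 SD, the range is 0.071 / 1.133 = 6% to 0.238 / 1.133 = 21%.

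**4. Type I error in the same kind of scenario.** Simulation with no true effect, 21 per arm, 40,000 runs, two-sided t-test at 5%, leavers from the study arm only. The correlation is between the tendency to leave and a poor outcome.

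| Leavers | Correlation 0 | Correlation 0.5 | Correlation 1 (worst case) |
|---|---|---|---|
| 3 | 5.0% | 6.8% | 14.5% |
| 6 | 5.1% | 10.3% | 31.9% |

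With no link between leaving and outcome, the error rate stays at its nominal level and the mean difference is unbiased.

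**5. Does the fix need more patients?** With outcomes from all 42 (21 per arm), power at the planned effect is 0.948, against 0.910 for 36. It does not.

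**The case against.** The strongest reply is that the protocol nowhere says early leavers are dropped. The sentence keeps in some patients who leave, and it can be read as a minimum under item 18b's broad promise. This stands in part: exclusion is implied and not written out, and item 18b is better described as a promise narrowed by its own rule than as a flat contradiction. It does not rescue the wording, because no section provides for patients at 2 weeks or less.

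A reader might go further and infer that the result will be biased in favour of the intervention, because the Discussion concedes that "the ADIM technique is slightly difficult to operate and subjects have difficulty understanding the treatment" and early leaving should therefore be commoner in the study arm. The documents do not support this. The Discussion calls the technique only slightly difficult, does not say that patients will leave, and plans repeated education in response; item 11c adds education for the trial group. Item 10 requires an MMSE above 24 and excludes those unable to cooperate. Item 11a gives both arms 60-minute sessions (40 + 20 in the study arm), so session length does not explain extra losses. Unblinded control patients may leave too. The direction is undetermined.

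The scenarios are also one-sided. The 15% is attrition during the trial, not by week 2, and k = 5 places most of the roughly 6 expected losses early and in one arm.

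Finally, the absence of a named imputation method is not a fault here. It can be left to an analysis plan that is not shown.

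**Conclusion.** The point holds in this form: as written, the rule makes recording and counting depend on time on treatment after randomisation, implies that patients with 2 weeks or less are neither followed up nor analysed, and so leaves an unblinded superiority comparison open to bias. Neither size nor direction can be derived from the documents. The 0.07 to 0.24 SD range illustrates what is at stake under stated assumptions (3 to 5 early leavers in the study arm, outcomes 0.5 to 1.0 SD worse, no matching control loss). It is not an estimate, and the bias is nil if leaving is unrelated to outcome. The matter is worth settling promptly: the Trial status section reports that recruitment is under way, and walking tests that are not recorded cannot be recovered.

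**What to change.** - Remove the more-than-2-weeks condition from items 18b, 19 and 20c.
- State in item 20c that all randomised patients are analysed in their allocated group.
- State in items 18b and 19 that the 4-week 10MWT is sought from, and recorded for, every randomised patient whatever the time on treatment.
- Keep the more-than-2-weeks set, if it is wanted, only as a sensitivity analysis. The method for outcomes that remain missing can be set in the SAP.

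The cost is an amendment to three sections, some effort to test patients who leave early, and a possibly less favourable estimate. The sample size does not change.

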### Plans to give access to the full protocol, participant level-data and statistical code {31c}

The results will be published in journals.

## Oversight and monitoring

### Composition of the coordinating center and trial steering committee {5d}

The trial steering committee, constituted of a cohort of seasoned professionals, assumes a critical obligation in safeguarding the scientific soundness, lucidity, and adherence to the clinical trial process. In the following sections, we delineate their compositional classification, functional allocation, and respective duties:1. Our trial steering committee is made up of the following members:A chairperson, who is a senior professional lead physicianSeveral medical experts or researchers, representing different subject areas, such as biostatistics and clinical practiceAn ethics expert.

2. RoleTo assess and review the design and conduct of clinical trials to ensure that they meet scientific ethical and regulatory requirementsDevelop and review documents such as clinical trial protocols, study protocols, informed consent forms, etc.Monitoring the progress and results of clinical trialsGiving professional advice and recommendations to assist in improving the quality and safety of trials.

3. The responsibilities of the trial steering committee include:Ensuring the scientific validity and safety of clinical trialsOverseeing ethical issues in the trial processProviding professional advice and opinions to assist investigators in resolving problems in trialsProtecting the rights and safety of trial participants.

### Composition of the data monitoring committee, its role and reporting structure {21a}

The data monitoring committee is a team of a range of professionals who monitor and assess the quality and integrity of data, data security, and confidentiality needs in clinical research. Its organizational structure and roles are as follows:1. The organizational structureA research data manager or a representative of the data management committee (DMC)Statisticians or professional data analystsPharmacologists or medical specialistsBiostatisticiansComputer scientists or information technology specialists

2. The role of the data monitoring Committee includes:Monitoring the integrity and quality of data in the studyReviewing data collection, documentation on data processing and data analysisOverseeing the processing and analysis of the dataChecking data to ensure compliance with the research plan and research protocolDealing with ethical and legal issues relating to dataConducting data and security assessments and ensuring compliance with relevant regulations.Protecting the security and confidentiality of data

### Adverse event reporting and harms {22}

Details of the operation are in the “Criteria for discontinuing or modifying allocated interventions {11b}” section.

### Frequency and plans for auditing trial conduct {23}

The appraisal of a trial’s execution is an essential aspect of the trial process. It includes protocol, interim, and end-of-trial reviews. The ethical committee and autonomous DMC scrutinize the trial protocol while the interim trial audits are examined on a yearly basis, and the end-of-trial audits are undertaken exclusively by the independent DMC. Adherence to trial protocol by the trial team, alongside the utilization of audit mechanisms and tools, are indispensable to ensure scientific integrity and precision of the trial outcomes.

### Plans for communicating important protocol amendments to relevant parties (e.g., trial participants, ethical committees) {25}

Any modifications to the study protocol that possess the potential to influence patient safety, the investigation’s execution, or the potential benefits bestowed upon patients, including adjustments to the research objectives, design, or significant intervention administration, will be subject to solicitation for evaluation and expert analysis. These evaluations will transpire through well-established channels of communication with pertinent personnel, whereby the suggestions and proposed alterations will be meticulously scrutinized. Any formal modifications to the protocol that adhere to the highest standards of clinical trial design and ensure the rationality and validity of the study protocol will be efficiently implemented.

### Dissemination plans {31a}

At the end of the trial, we will take the following steps to communicate the results of the trial:Dissemination of trial findings to participants will be conducted via telephone at the end of the study period. Comprehensive explanations of the trial’s objectives, results, conclusions, and recommendations will be provided by the researchers during the telephone communication.The communication of research outcomes to healthcare professionals will be facilitated through diverse means such as dissemination in reputable journals, presentation at scholarly conferences, and engagement in online forums and workshops.In order to ensure scientific integrity and data rigor, trial findings are presented for evaluation to a data monitoring committee or an intellectual property protection agency. Publication of the results is only considered after receipt of constructive feedback and verification by the aforementioned entities.

## Discussion

The study expects to investigate the effects of DBM combined with ADIM on balance capacity, walking function, and quality of life in early to mid-stroke patients.

Patients with stroke often experience weakened trunk muscles, which leads to impaired balance, reduced ability to shift their center of gravity, and limited walking function. A previous study has shown a positive effect of enhanced core stability on walking function in patients with stroke [20]. Therefore, this current study aims to utilize DBM combined with ADIM training to activate the core muscles of the trunk, improve abdominal muscle strength, and enhance trunk stability in patients with stroke, thereby improving their balance and walking function and improving their quality of life.

In everyday life, the voluntary contraction of the human trunk muscle groups counteracts some of the instability of distal limb movements and unpredictable disturbances from the external environment. During locomotion or ambulation, the core musculature is sequentially activated prior to the activation of peripheral limb muscles, facilitating the smooth execution of non-vigorous movements [21]. Motor control of the trunk is highly influential in distal limb movement and is associated with functional movement in individuals [9]. The significance of core muscle strength in relation to maintaining body balance and walking function is clearly evidently.

The core muscles are concentrated in the trunk and lower limb areas of the body. It plays an important role in trunk stabilization, walking initiation, and fall prevention [22, 23]. The transversus abdominis muscle, a band-like structure situated within the abdominal region, extends across multiple joints and serves as a pivotal motor hub for the limbs and head within the core area. Its strength directly affects the movement of the distal limbs of the body [7]. Notably, combining breathing training with core training yields better results in improving trunk stability compared to single-factor interventions such as core training [24]. The diaphragm is a key muscle in the study of breathing training. In combination with the transversus abdominis, the diaphragm is effective in maintaining spinal stability through the adjustment of intra-abdominal pressure [25]. Based on these findings, this trial aims to investigate the effect of DBM combined with ADIM on the rehabilitation of patients with stroke in terms of balance and walking function.

Previous studies on core stroke training have predominantly relied on scales or instruments to evaluate patients’ balance or walking function. Although these assessments are effective in assessing patients’ function, they make it difficult to further explain the site of action of the intervention in scientific studies and are not conducive to an in-depth study of the mechanism of action of the treatment. In contrast, musculoskeletal ultrasound has the advantages of portability, dynamic observation, and no radiation and is simpler to perform than ultrasound in the diagnostic department [26, 27]. In recent years, there has been an increase in studies on the use of ultrasound to observe morphological changes in the diaphragm and transversus abdominis muscle [28]. According to recent reports, ultrasound can effectively reflect changes in diaphragm thickness and mobility [29]. In 2015, Kapping found that ultrasound observation of transversus abdominis thickness in the clinical setting had reliable reliability and validity through a rigorous trial comparison [26]. Based on the above, this study will use musculoskeletal ultrasound to observe and measure morphological changes in the diaphragm and transversus abdominis muscles before and after the trial, combined with scales for balance and walking function, to assess the effect of the intervention in both morphological and functional terms.

The 10MWT, a commonly used instrument for assessing ambulation in stroke survivors, plays a pivotal role in objectively measuring walking speed, gait stability, and overall restoration of walking function [12, 30]. Research has demonstrated that the 10MWT exhibits favorable reliability and validity, thereby providing dependable data to facilitate the monitoring and advancement of rehabilitation interventions [31]. Additionally, the high sensitivity of the 10MWT enables the identification of even subtle enhancements in ambulatory ability. Consequently, it serves as a crucial tool for tracking alterations in walking function specifically in patients with stroke. Given these considerations, we selected the 10MWT as the primary outcome measure for this study.

There are still some limitations to this study due to some objective reasons: (1) strict control of inpatients in hospitals due to the epidemic situation, with a relatively homogenous source of subjects; (2) the ADIM technique is slightly difficult to operate and subjects have difficulty understanding the treatment; (3) unlike medication, rehabilitation training necessitates technical expertise and therapist guidance, making it challenging to implement double-blind protocols.

To adequately address the aforementioned limitations and minimize experimental errors, this study will implement the following measures: (1) it is difficult to conduct multicenter studies under strict epidemiological control, and when collecting cases in our hospital, we try to collect patients with stroke with different causes that meet the inclusion criteria; (2) multiple pre-intervention educations on ADIM techniques for therapists and subjects; (3) to minimize potential bias in trial outcomes, distinct personnel will be assigned for trial randomization and outcome assessment, ensuring the maintenance of single blinding.

Patients with stroke often have reduced trunk stability due to a lack of core strength, which in turn impairs walking function. To address this issue, our trial aims to focus on activating two critical core muscle groups, namely the diaphragm and transversus abdominis, through a combination of DBM and ADIM. Based on this training, which increases abdominal pressure and improves trunk stability, this trial will further investigate the extent to which this training improves balance and walking function in patients with early to mid-stroke.

